#### Statistical analysis

Analyses will be based on the principle of intention-to-treat. Descriptive statistics will be used to summarize patient characteristics and endpoints separately in each of the treatment groups. Estimates in each group will be reported by percentage experiencing RITL together with the corresponding 95%CI.

Exploratory analyses investigating association of clinical/patient/planning factors on outcomes will be performed using standard statistical methods (t-test, multivariate regression methods, and chi-squared tests). Time-to-event outcomes will be described using the method of Kaplan-Meier and any exploratory comparisons using logrank tests and proportional hazards regression. No imputation will be made for missing data. Estimation of the relationship between DVH parameters and toxicity will be evaluated using regression methods and correlations between functional and conventional DVH parameters will be evaluated. All patients who are randomised will be included in the analysis of safety and efficacy outcomes. Any patient who is randomised but does not receive radiotherapy based on the intervention allocated treatment plan will be described in detail along with the reason for not receiving the prescribed treatment.

#### Data safety monitoring committee and interim analysis

The data safety monitoring committee will consist of a statistician, an independent investigator, and a data manager from Clinical Trial Unit. The committee will review serious adverse events on annual basis. An interim analysis for futility is proposed to be performed after 50 patients randomised to SPECT have completed treatment and have been followed for at least 6 months. The futility boundary is determined from a likelihood ratio approach which suggest that if the ‘support’ for the interesting rate based on the likelihood ratio (84% rate: 75% rate) is LR ≤ 0.125 then the study could be considered futile in its ability to yield an estimate consistent with a freedom from RILT of at least 84%. For 50 patients, fewer than 35 patients are free from RILT, the LR ≤ 0.065. If this is observed, consideration will be given to either (i) modify the protocol (inappropriate control rate); (ii) alter the study design or (iii) stop the study. An independent Data Safety and Monitoring Committee will oversee the safety of the study as well as review the results of the 50-patient futility analysis. Otherwise, the study would proceed to recruit an additional 80 patients in Arm 1. Arm 2 would recruit in all 65 patients.

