### Statistical considerations

#### Sample size

Bases on the Quantitative Analyses of Normal Tissue Effects in the Clinic lung report and previously reported prospective trial rates [6], a freedom from RILT rate of 75% would be expected to be observed in patients receiving standard therapy. For the SPECT to be considered worthwhile for further investigation a freedom from RILT rate of at least 84% would suggest a clinically worthwhile signal in SPECT. Based on Ahern’s single arm design, a sample size of 130 patients receiving SPECT would have at least 80% power to have 95% confidence in ruling out an uninteresting freedom from RILT rate of 75% in favour of a clinically more interesting rate of 84%. In order to reduce selection bias, a randomised phase II design is proposed with a 2:1 randomisation of SPECT to standard treatment. The sample size of 195 is required and a total of 200 patients will be enrolled to offset a modest attrition rate. All patients will be followed for at least 6 months. The primary endpoint will be described by the proportion of patients in the SPECT arm are free of symptomatic RILT of at least grade 2 together with the associated 95% confidence interval. The corresponding proportion will be calculated in the control arm to provide contemporary free of symptomatic RILT of at least grade 2 rates in the standard treatment group.

It is expected that 5–6 patients per month can be accrued between the two participating countries (Denmark and Australia), thus, it is expected that accrual to this study could be completed in 3 years.

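### The interim futility rule contradicts itself: LR ≤ 0.125 means 36 or fewer RILT-free of 50, but the printed count means 34 or fewer

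*Protocol article*

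**What the plan says.** The protocol article, under Data safety monitoring committee and interim analysis, plans one futility look, to be done "after 50 patients randomised to SPECT have completed treatment and have been followed for at least 6 months". The boundary is put on the likelihood-ratio scale, comparing the two design rates: "84% rate: 75% rate) is LR ≤ 0.125 then the study could be considered futile". The next sentence converts this to a count: "For 50 patients, fewer than 35 patients are free from RILT, the LR ≤ 0.065". The action follows directly: "If this is observed, consideration will be given to either (i) modify the protocol (inappropriate control rate"), with altering the design or stopping as the other options. Otherwise Arm 1 goes on to recruit 80 more patients. The two rates are those of the Sample size section, which aims at "ruling out an uninteresting freedom from RILT rate of 75% in favour of a clinically more interesting rate of 84"%. The article does not say whether the ratio or the count governs, and does not explain the step from 0.125 to 0.065.

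**The concern.** A likelihood-ratio threshold for two fixed rates and a fixed number of patients corresponds to exactly one count. The article gives all four ingredients (two rates, direction of the ratio, 50 patients, threshold), so the count can be checked, and it does not follow from the threshold. This is the only interim decision rule in the document. The committee could see a result that meets one criterion and not the other, and would then have to choose between them with the data in view. At stake is whether an ineffective arm is flagged after 50 patients or continues to 130.

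**Working it through.** **Inputs.** From Sample size: interesting RILT-free rate 0.84, uninteresting rate 0.75. From the interim section: ratio taken as 84% over 75%, 50 SPECT patients, futility at a ratio of 0.125 or less, and a trigger count of fewer than 35, that is x ≤ 34.

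**Formula.** For x RILT-free of 50 the binomial coefficient cancels:

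LR(x) = (0.84/0.75)^x × (0.16/0.25)^(50−x) = 1.12^x × 0.64^(50−x).

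Each extra RILT-free patient multiplies the ratio by 1.12/0.64 = 1.75.

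**The plan's own figure.** LR(35) = 1.12^35 × 0.64^15 = 0.0654. The printed 0.065 is reproduced at x = 35, which confirms the formula. That value is outside the printed count, which begins at 34.

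**Ratio and probability of meeting each boundary (exact binomial, n = 50).**

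| RILT-free x | LR(x) | LR ≤ 0.125? | x < 35? | P(X ≤ x), true 75% | P(X ≤ x), true 84% |
|---|---|---|---|---|---|
| 34 | 0.0374 | yes | yes | 16.3% | 0.4% |
| 35 | 0.0654 | yes | no | 25.2% | 1.0% |
| 36 | 0.1144 | yes | no | 36.3% | 2.2% |
| 37 | 0.2002 | no | no | 48.9% | 4.8% |

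Solving for the threshold: x ≤ (ln 0.125 − 50 ln 0.64) / ln 1.75 = (−2.079 + 22.314) / 0.5596 = 36.16, so the stated threshold means 36 or fewer.

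**Conflict zone.** The criteria disagree at x = 35 and x = 36. The probability of landing there is 36.3% − 16.3% = 20.0% at a true 75%, and 1.9% at a true 84% (2.23% − 0.38%).

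**Other readings tried at 50 patients and 84%/75%.** None puts the 0.125 cut-off at 34 or 35:
- Normal-approximation likelihood ratio: 0.043 at 35 and 0.091 at 36.
- 84% against the observed rate: 0.048 and 0.102.
- Ratio of cumulative tail probabilities: 0.038 and 0.062.

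**Effect on the final analysis.** The article prints no final success count. As a derived assumption, success at 106 or more of 130 gives one-sided alpha 0.049 and power 81.4% without an interim look, consistent with the design as described. If the study always stops when the boundary is met, power is 81.3% with x ≤ 34 and 80.9% with x ≤ 36; one-sided type I error is 0.0491 and 0.0485.

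**The case against.** The strongest reply is that the rule is advisory. The study could be considered futile, options will be considered, nothing forces a stop, and the committee includes a statistician who can compute the ratio for any count. That stands as a limit on the consequence: at 35 or 36 the choice is between deliberating and proceeding, not between stopping and proceeding. An advisory rule must still say when deliberation is due, and here it says so in two ways.

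Second, the count sentence is literally true. Every count below 35 has a ratio of at most 0.037, so it is also below 0.065, and every count it flags meets 0.125 as well. On this view 0.065 is a loose upper bound and the count only an example of strong evidence. The inequality is indeed true, and there are two competing cut-offs in practice, 36 and 34. But the sentences on what happens if this is observed, and what happens otherwise, make the count the operative trigger. If they refer back to 0.125 instead, the printed count misleads. Either way the text needs correcting.

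Third, the article does not say which criterion was intended, so 36 cannot simply be declared right. That is fair, and the fix allows for it.

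Fourth, power and type I error barely move, and the 20.0% applies at a true rate of exactly 75%. Both points are correct. The cost lies in how often an ineffective arm goes on to full accrual, which is what a futility look is meant to limit.

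**Conclusion.** The point holds; the rule is wrong as written. The stated threshold of 0.125 gives 36 or fewer RILT-free of 50, and the stated count gives 34 or fewer. Nothing else in the article reconciles them. At a true rate of 75% the count flags futility less than half as often as the threshold (16.3% against 36.3%), and the two disagree in one trial in five. At a true 84% both rarely trigger.

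The boundary result rests only on figures printed in the article and the binomial likelihood. The power comparison also assumes a final cut-off of 106 of 130 and that the boundary is followed as a stopping rule. This must be fixed because it concerns the trial's only interim decision rule and cannot be settled credibly once the interim data are known.

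**What to change.** Decide which criterion governs and make the other agree with it, in the protocol and the committee's charter, before the 50-patient look.

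- **If the 0.125 threshold governs:** state that, of 50 patients, 36 or fewer free from RILT meets the criterion (ratio about 0.114 at 36) and 37 does not (ratio 0.200).
- **If a lower count was intended:** restate the ratio threshold to match, about 0.037 for 34 or fewer or about 0.065 for 35 or fewer. Round the threshold up, to 0.038 or 0.066, because the unrounded ratios are 0.0374 and 0.0654 and a threshold rounded down would exclude the count it is meant to include.

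In either case, give the probability of meeting the boundary at true rates of 75% and 84%, so that the committee knows how the rule behaves.

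The cost is one sentence. Moving from the printed count to 36 or fewer lowers power by about 0.4 points (81.3% to 80.9%), still above the planned 80%, and the sample size does not change.

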#### Ethics approval

This protocol and the template informed consent forms have been reviewed and approved by the sponsor and the applicable ethical committee of each participating research centre with respect to scientific content and compliance with applicable research and human subjects’ regulations. The responsible investigator will ensure that this study is conducted in agreement with the Declaration of Helsinki. Written informed consent will be obtained from all patients for the acquisition and use of anonymized clinical data before they are recruited. All personal health information will be kept strictly confidential. All participants will be identified using initials and a unique identification number. Confidential subject identification list will be kept at Clinical Trial Unit. Trial Management Committee will oversee the intra-study data sharing process. All lead Investigators will be given access to the cleaned data sets. Project data sets will be password protected. Principal investigator will have direct access to all site’s data sets. To ensure confidentiality, data dispersed to project team members will be blinded of any identifying participant information. Published data will not contain any identification information of participants. Randomised controlled trial shall be presented according to the CONSORT guidelines. Regardless the outcome of the trial, positive, negative, and inconclusive results will be published. Preliminary results are expected after interim analysis. Authorship of the trial abstract and manuscript will be decided by the principal investigator at the time of submission. The Investigator will make safety and progress reports to the Ethics Committee annually and within 3 months of study termination or completion at their site. These reports will include the total number of participants enrolled and summaries of each safety and efficacy review.

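### The publication text expects preliminary results after a futility-only interim, while much recruitment and most 12-month toxicity scoring are still open, and nothing keeps those results with the monitoring committee

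*Protocol article*

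**What the plan says.** The section on the data safety monitoring committee states the purpose of the look: "An interim analysis for futility is proposed". It is to be "performed after 50 patients randomised to SPECT have completed treatment and have been followed for at least 6 months". The committee is to "review the results of the 50-patient futility analysis". If the boundary is met, the options are to modify the protocol, alter the design or stop. If not, the text continues: "Otherwise, the study would proceed to recruit an additional 80 patients in Arm 1". Arm 2 is to reach 65.

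The Ethics approval section also holds the publication text. It promises "Regardless the outcome of the trial, positive, negative, and inconclusive results will be published", and the next sentence is "Preliminary results are expected after interim analysis". The sentence after that deals with authorship of the abstract and manuscript.

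No sentence in the article confines interim results to the committee, makes their release conditional on stopping, or delays it until scoring is complete. On data access the same section says "Principal investigator will have direct access to all site’s data sets".

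**The concern.** A futility look needs no audience outside the monitoring committee. If its results circulate while the trial runs, patients, referrers and toxicity scorers learn how the trial is going before most outcomes are in. The endpoint includes grade 2 or worse dyspnea and cough under CTCAE version 5 (Endpoints), and such grading leaves room for judgement.

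The design adds to the exposure. The trial is described as non-comparative (Study design), and success is judged on the SPECT-arm proportion against a fixed 75% (Sample size). In a comparative trial, a drift common to both arms would largely cancel. Here it goes straight into the estimate. Upward drift in the proportion scored free of toxicity would favour a false success, and downward drift would cost power. Patients scored before and after the release are pooled in one proportion.

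**Working it through.** **1. The plan's own figure.** Inputs from Sample size: null 75%, alternative 84%, 95% confidence, at least 80% power. With an exact binomial test at one-sided 0.05, the smallest n that meets both conditions is 130, with success at 106 or more free of toxicity:

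- P(X ≥ 106 | 130, 0.75) = 0.049
- P(X ≥ 106 | 130, 0.84) = 0.814

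This reproduces the stated 130. The article does not print the threshold of 106; it follows from this calculation.

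**2. When the interim matures.** Inputs: 50 SPECT patients, 2:1 allocation, 5–6 patients per month and 6 months of follow-up, all from the article. The 1.25–1.75 months of radiotherapy is an assumption, as are prompt treatment after randomisation and no pause in accrual.

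- Randomised when the 50th SPECT patient enters: 50 × 3/2 = 75
- Time to reach 75: 75/6 = 12.5 months to 75/5 = 15 months
- Interim mature: 12.5 + 1.25 + 6 = 19.75 months to 15 + 1.75 + 6 = 22.75 months

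**3. What is still open then.**

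- Enrolled: between 5 × 22.25 = 111.25 and 6 × 20.25 = 121.5
- Still to enrol out of 200: between 78.5 and 88.75, so about 78–89
- Through 12 months after radiotherapy (radiotherapy duration cancels): 5 × (15 + 6 − 12) = 45, or 6 × (12.5 + 6 − 12) = 39
- Not yet through 12-month scoring: 200 − 45 = 155 to 200 − 39 = 161, counting those not yet enrolled

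**4. Sensitivity of the primary result.** The documents give no size for any drift, so the shifts are illustrative. Take a true rate of 75%. The first 50 SPECT patients follow Bin(50, 0.75) and the later 80 follow Bin(80, 0.75 + shift). False success is a sum of at least 106.

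| Shift in later 80 | P(false success) |
|---|---|
| 0 | 4.9% |
| 1 point | 6.8% |
| 2 points | 9.1% |
| 3 points | 12.0% |
| 5 points | 19.9% |

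The figure 80 is 130 − 50. On the timing above, some of those 80 are already enrolled and partly scored. If only the SPECT patients not yet enrolled shift (two thirds of 78–89, or about 52–59), a 3-point shift gives about 9–10%.

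**The case against.** **The sentence does not say what is released, or to whom.** It says results are expected, not published. It could mean the ethics reports described later in the same section, which are to summarise each safety and efficacy review, or publication only if the trial stops. A reader might infer that rates by arm will be published; the text does not say so. This stands, and the point has to be put as the likeliest reading. That reading rests on the neighbouring sentences, on publication before and authorship after.

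**A condensed article may leave confidentiality rules to the full protocol or a committee charter.** That is a fair answer to silence alone. Here, however, the article makes a positive statement that points towards release.

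**Patients and care staff are blinded to arm.** The allocation goes to staff outside direct care and study assessments (Randomisation and blinding procedures). A blinded scorer who knows an interim rate still does not know who received SPECT, so differential scoring is limited. The concurrent control arm would also make a general drift partly visible. Both arguments stand. They do not remove the problem, because the formal criterion compares the SPECT arm with 75% and makes no correction from the control arm. The treating oncologist may also be unblinded for a serious adverse event or an adaptation.

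**Who scores is not fixed.** A reader might assume that treating physicians grade all the follow-up toxicity. The article names a physician for the on-treatment visits but does not say who scores from 1 to 12 months.

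**Conclusion.** The point holds as a weakness in wording that is cheap to repair. Followed in its likeliest sense, the sentence puts interim outcomes into circulation with about 78–89 of 200 patients still to enrol and about 155–161 not through 12-month scoring. These counts rest on the planned accrual rate, the assumed radiotherapy duration and uninterrupted recruitment.

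The bias is conditional and its size cannot be derived from the documents. The rise from 4.9% to between 6.8% and 19.9% shows how sensitive the criterion is to shifts of 1–5 points in the later 80 SPECT patients; it does not predict what would happen.

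Two stronger readings are not supported. A reader might apply a 3-point shift to all 130 SPECT patients and obtain P(X ≥ 106 | 130, 0.78) = 19.4%. The first 50, however, had the data that formed the interim scored before any release, so 12.0% is the matching figure for 3 points. A reader might also infer an inflated planned type I error. The look has no efficacy stop, so alpha spending is not at issue. The concern is the integrity of the data collected afterwards.

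**What to change.** Replace the sentence in the Ethics approval section with:

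> Interim outcome results are confidential to the DSMC, which gives the trial management committee only its recommendation (continue, modify the protocol, alter the design, or stop). No outcome results, by arm or pooled, are presented or published before the primary analysis, unless the trial stops early.

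The four recommendations match the options already listed in the interim section. Pooled results are included because the drift at issue does not need knowledge of arm. If the sentence was meant only for ethics committee reporting or for non-outcome data, the text should say so, and the ethics reports should be worded to agree with the new rule.

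Sample size, boundary, recruitment and conduct are unchanged. The cost is the loss of an early abstract.

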## Discussion

Over the last two decades, various functional modality techniques have been investigated for use in lung cancer RT, such as perfusion/ventilation SPECT, 4DCT (ventilation), hyperpolarized ^3^He Magnetic resonance imaging (MRI) (ventilation), Gallium-PET (perfusion/ventilation) and hyperpolarized ^129^Xe MRI [11, 13–15]. As lung function consists of three components- airways ventilation, gas exchange in alveoli and perfusion of blood vessels, ideally, combined imaging of perfusion and ventilation, will provide the most accurate imaging of pulmonary function. Never-the-less for RT planning purposes, perfusion imaging appears to be sufficient [16–18]. Indeed, perfusion imaging is the most commonly used form of functional lung imaging reported in the literature [8]. In regard to the lung function assessment for RT of lung cancer and other types of cancers involving thoracic irradiation (e.g. breast cancer, cancer in chest wall, lymphomas), perfusion has shown a predictive potential for radiation-induced toxicity in a consistent dose-response relation [19–24]. Considering our previous expertise in establishing the role of SPECT in radiation-induced lung injury, and multi-centre experience incorporating functional avoidance into RT planning, SPECT/CT imaging was found to be most feasible and pragmatic functional imaging for the ASPECT trial.

The results of the inter-institutional comparability planning study show that standard and functional avoidance plans are comparable between the centres (Additional file 1). Dose planning objectives were met in 4 out of 5 patients. Both centres performed standard planning with minimal difference in PTV coverage. Some differences were observed in doses to total lung and heart. Functional planning objective of minimizing dose to the functional lung without significant dose increase to organs at risk was achieved for 4 out of 5 patients. For one patient standard dose planning constraints, as well as functional objectives were not achieved at one centre due to large target volume (PTV volume 616 cm^3^). Differences between Centre 1 and Centre 2 standard and functional plans (∆ Standard and ∆ Functional) were acceptable. Dose reduction to FL, achieved by functional avoidance plans for Centre 1 and Centre 2 were comparable. As shown in Supplementary Table S1, dose reduction to FL was comparable to the previously published results [8, 12].

The ASPECT trial will be the first randomised clinical trial incorporating SPECT/CT functional imaging into radiotherapy of lung cancer assessing the clinical outcomes. The project will be of great international significance, as methods to improve the treatment outcome of lung cancer patients are warranted worldwide. If successful, the trial has a potential to improve the treatment of lung cancer and broaden the category of patients receiving radiotherapy. The trial can potentially lead to tumour dose intensification and further improve patients’ prognosis.

In summary, ASPECT trial will investigate functional avoidance method of RT in clinical practice, and will establish toxicity outcomes for patients with lung cancer undergoing curative chemo-RT.

